## Abstract

**Introduction::**

Hypertension patients often suffered from insomnia problems which lowered the quality of life. Studies have shown that acupuncture is effective to treat perimenopausal and cancer-related insomnia. However, there is a lack of randomized controlled trials to support the effectiveness of acupuncture on insomnia of hypertension patients.

**Methods and analysis::**

This study is a randomized, double-blind (patients and evaluators), and placebo-controlled clinical trial to investigate the effect of acupuncture in hypertension patients’ insomnia management. We will recruit 158 hypertension patients suffering from insomnia in Bao’an People's Hospital, Shenzhen and randomly assign them into treatment group (antihypertensive drugs + acupuncture) and control group (antihypertensive drugs + sham acupuncture) in a 1:1 ratio. The patients will receive acupuncture 3 times a week for 12 weeks, and then a 6-months follow-up will be conducted after the treatment. The primary outcome is the Pittsburgh Sleep Quality Index. The secondary outcomes include sleep parameters, blood pressure dropping, sleeping pill dosage, Rating Depression Scale score, and Self-Rating Anxiety Scale score. The primary outcome will be evaluated at baseline, 4, 8, and 12 weeks, and 1, 3, and 6 months following the end of treatment. The secondary outcomes will be assessed at baseline and 12 weeks of the treatment period.

## Introduction

1

Hypertension is a common chronic disease, and it is estimated that 972 million (26.4%) adult hypertension patients in 2000 will increase to 1.56 billion (29.2%) in 2025 worldwide.^[1]^ Hypertension often causes dizziness and headache, leading to several insomnia problems such as difficulty in falling asleep, easily waking up at night, or low sleep efficiency.^[2]^ Insomnia reduces productivity, lowers life quality, and impairs cognitive and emotional functions.^[3]^ If without proper treatment, insomnia can be developed as a chronic disease and increases the incidence of hypertension.^[4]^ Therefore, it is important to explore the adequate therapy to improve the insomnia of hypertension patients.

Currently, drug therapy and psychotherapy are the main methods to treat insomnia; however, psychotherapy exists some problems, such as the shortage of therapists and heavy economic burden for patients. Simultaneously, most drugs mainly effect on anti-anxiety, sedation and hypnosis, and long-term use may produce adverse reactions and drug dependence.^[5]^ In addition, it is easy to relapse or appear withdrawal symptoms after drug stopping.^[6]^ Acupuncture is an important part of traditional Chinese medicine, and has been widely used in China and some western countries. Presently, more and more attention has been paid to the clinical effect of acupuncture on insomnia. Study has showed that acupuncture increases the percentage of slow-wave sleep to improve the sleep quality.^[7]^ Fu et al^[8]^ have studied the effectiveness of acupuncture on perimenopausal insomnia, and found that acupuncture increased sleep efficiency and sleep time, decreased wakefulness, and improved sleep structure, showing that acupuncture could improve the insomnia from both subjective and objective aspects. Yin et al^[9]^ also found a good effect of acupuncture on the improvement of primary insomnia. To our best knowledge, whether acupuncture could be effective on the insomnia of hypertension patients has not been reported.

Given the lack of studies on acupuncture in hypertension patients’ insomnia management, we conducted a randomized, double-blind, and placebo-controlled trial so as to evaluate the efficacy and safety.

## Methods and analysis

2

### Study design

2.1

This study is a randomized, double-blind, and placebo-controlled trial to evaluate the efficacy and safety of acupuncture on hypertension patients’ insomnia management, and the flow chart of this trial is displayed in Figure 1. The trial will be performed in Bao’an People's Hospital, Shenzhen. The study has been approved by the Ethics Committee of Bao’an People's Hospital, Shenzhen (BYL20210904), and registered on www.chictr.org.cn (ChiCTR2100051063).

**Figure 1 F1:**
[figure not shown]
The flow chart of trial process.

### Patients

2.2

The hypertension patients with insomnia will be recruited in Bao’an People's Hospital, Shenzhen from September, 2021 to March, 2022. Each patient uses 1 to 3 antihypertensive drugs (calcium antagonist, angiotensin converting enzyme inhibitor/angiotensin receptor blocker, diuretics, or β-blocker). On the basis that patient's diet, physical activity, and use of antihypertensive drugs remain unchanged, they will accept a 12-week treatment. Each patient is required to sign the informed consent before the treatment, and accept a 6-month follow-up (visits at 1, 3, 6 months).

### Inclusion criteria

2.3

The patients should meet all the following criteria:

age between 18 and 75 years;meeting the diagnostic criteria of hypertension (systolic blood pressure 140-180 mm Hg and/or diastolic blood pressure >90 mm Hg);insomnia diagnosed in accordance with the International Classification of Sleep Disorders^[10]^;Pittsburgh Sleep Quality Index (PSQI) score >5;not receiving acupuncture for at least 1 year;agreeing to participate in this clinical study and signed the informed consent.

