### Exclusion criteria

2.4

The patients will be excluded if they meet 1 of the following criteria:

with secondary hypertension;with severe complications, such as cardiovascular events, endocrine disorders, renal, and hematopoietic system disease;with comorbidities including cancer and mental illness;pregnant or lactating women;having skin infections near the specified acupoints;with insomnia caused by external environment disturbances;with severe chronic obstructive pulmonary disease and bronchial asthma;with severe neurological dysfunction;with alcohol abuse or drug dependence;who considered by the researcher to be unsuitable for this study.

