### Patients’ safety

2.10

All patients will accept blood routine, hepatic, and renal functions tests to identify and exclude the patients with severe heart, liver, or kidney disease after the recruitment and before the random allocation. The acupuncture will be discontinued if patients occur any adverse effects. Adverse events (AE) indicate any adverse medical events that occur in the patients regardless of events are related to the operation or experimental drug in the study. The patients will be informed to contact the doctor to diagnose and treat the AE. Fainting, allergy, and pain may appear in the acupuncture clinical trials.^[15]^ If faints occur, the needles will be pulled out immediately, patients will be returned to supine position, given warm or sugar water, and rest until complete recovery. If allergy or pain occurs, needles are taken out immediately and patients are treated according to the specific situation.

The serious AE (SAE) includes death, life-threatening conditions, severe or persistent incapacity or disability, hospitalization, extension of hospitalization time, and potentially serious events. Whether relating to the trial, any SAE or relevant events must be reported to the research unit within 24 hours. The researcher is responsible for recording and reporting all AE and SAE that occurred during the trial (including a 12-week treatment period and a 6-month follow-up period) since the date of signing the informed consent.

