### Withdrawal criteria

2.11

The patients presenting the following conditions will be withdrawn from this study:

occurring serious adverse reactions so as to be inappropriate to continue the study;occurring severe complications or condition deterioration so as to need emergency measures;not following the prescribed treatment or without complete data so as to affect the efficiency of evaluation.

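### The 180 mm Hg systolic limit sits in one branch of an and/or, so it does not apply once diastolic exceeds 90: 190/85 fails the criterion, 190/95 and 200/125 meet it

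*Protocol article*

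**What the plan says.** Section 2.3 (Inclusion criteria) opens with "The patients should meet all the following criteria". The blood pressure item, given as the diagnostic standard for hypertension, reads "systolic blood pressure 140-180 mm Hg and/or diastolic blood pressure >90 mm Hg".

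Four other sections bear on very high pressure. None of them states a blood pressure value.

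- **Section 2.4 (Exclusion criteria)** removes secondary hypertension, patients "with severe complications, such as cardiovascular events, endocrine disorders, renal, and hematopoietic system disease", and anyone "who considered by the researcher to be unsuitable for this study".
- **Section 2.10 (Patients' safety)** uses blood, liver and kidney tests "to identify and exclude the patients with severe heart, liver, or kidney disease after the recruitment and before the random allocation". It also stops acupuncture if adverse effects occur.
- **Section 2.11 (Withdrawal criteria)** withdraws patients for serious adverse reactions, for "occurring severe complications or condition deterioration so as to need emergency measures", and for departing from the prescribed treatment or having incomplete data.
- **Section 2.2 (Patients)** has participants on one to three blood pressure drugs, with diet, activity and drug use held constant: "use of antihypertensive drugs remain unchanged, they will accept a 12-week treatment".

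**The concern.** An upper figure of 180 in an entry criterion looks like a limit on how high a patient's pressure may be. Joined by and/or to a diastolic condition with no upper bound, it limits only patients whose diastolic is 90 or below. At a systolic of 190, the patient with the higher diastolic is accepted and the one with the lower diastolic is refused. The article gives no reason for that ordering.

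Two things are at stake:

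- **Safety.** A patient accepted this way would have 12 weeks of study treatment with blood pressure drugs meant to stay as they are.
- **Consistent screening.** A screener applying the printed words and one applying the likely intent could decide 190/95 differently.

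**Working it through.** The plan derives no figure from this criterion. Its sample size of 79 per group does not use blood pressure and plays no part here.

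**Inputs.** S is systolic and D is diastolic pressure in mm Hg. The thresholds 140, 180 and 90 are those of section 2.3. The and/or is read inclusively. The reading is assumed to be the one taken at screening.

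**Rules compared.**

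- Printed: (140 ≤ S ≤ 180) or D > 90
- General ceiling: S ≤ 180 and (S ≥ 140 or D > 90)
- Printed plus the proposed exclusion: printed and not S > 180

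**Step 1, S ≤ 180.** The upper limit is already satisfied, so the printed rule reduces to S ≥ 140 or D > 90. The general ceiling reduces to the same expression. The two agree.

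**Step 2, S > 180.** The systolic branch is false, so the printed rule reduces to D > 90. The general ceiling refuses everyone. The two differ exactly when D > 90.

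**Step 3, specific readings.**

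| Reading | Printed rule | General ceiling | Printed plus exclusion |
|---|---|---|---|
| 170/85 | meets | meets | meets |
| 135/95 | meets | meets | meets |
| 181/90 | fails | fails | fails |
| 181/91 | meets | fails | fails |
| 190/85 | fails | fails | fails |
| 190/95 | meets | fails | fails |
| 200/125 | meets | fails | fails |
| 170/130 | meets | meets | meets |

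At a systolic of 181, one extra millimetre of diastolic pressure (90 to 91) turns a refusal into an acceptance.

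**Step 4, the correction.** For S ≤ 180 the added exclusion changes nothing. For S > 180 it refuses everyone. It therefore reproduces the general ceiling at every reading. A check of all whole-number pairs with systolic 100 to 240 and diastolic 50 to 140 agrees. A count of such pairs depends on the grid chosen and says nothing about how often patients present with these values, so none is offered as a measure of size.

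**Step 5, other sections.** Sections 2.4, 2.10 and 2.11 work through complications, organ disease, adverse effects or judgement. None is triggered by a pressure value, so none brings the 180 limit back.

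**The case against.** **Intent.** The bracket explains a diagnosis, and and/or is normal in a diagnostic definition. The authors probably meant 180 as a general ceiling, and with a single hospital screening, staff may apply it that way. This lowers the weight of the point but does not remove it, because the printed rule does not say so. If 180 was not meant as a ceiling, refusing 190/85 while accepting 190/95 has no stated reason.

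**Existing safeguards.** These are real. A reading of 200/125 is an obvious candidate for the researcher's discretion under section 2.4. Table 1 schedules vital signs and an electrocardiograph at screening, and adverse events are followed throughout. Meeting the blood pressure item is therefore not the same as being enrolled. But discretion sets no fixed value, and 190/95 is a less obvious case for it.

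**Partial remedy.** A systolic exclusion leaves diastolic open, and 170/130 stays eligible. That is true. Whether to cap diastolic is a clinical choice, because the article states no diastolic limit to restore.

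**Stronger readings that a reader might infer.**

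- *The limit fails for everyone raised on both measures.* It does not: 170/95 is raised on both and lies within it. The gap needs systolic above 180 together with diastolic above 90.
- *Pressure goes unwatched during treatment, so week 4 and week 8 readings must be added.* The abstract does say "The secondary outcomes will be assessed at baseline and 12 weeks of the treatment period", and blood pressure change is one of those outcomes. But interim monitoring is operational detail that an article may leave to the full protocol, which is not shown. Its absence here is no fault.

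**Conclusion.** The point holds as a minor eligibility and safety correction. As printed, the 180 mm Hg limit does not apply to a patient whose diastolic exceeds 90, and nothing else in the article supplies a numeric ceiling.

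The gap is exactly systolic >180 with diastolic >90. The article does not give the share of screened patients in that region. That it is probably small is a judgement, not a result.

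The conclusion rests on an inclusive reading of and/or and on the article's text. A fuller protocol with a separate systolic exclusion would settle it. The documents do not show that such patients would in fact be enrolled, and no effect on the PSQI outcome or the sample size is claimed.

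**What to change.** Add one line to section 2.4 (Exclusion criteria): *systolic blood pressure >180 mm Hg*. Together with section 2.3 as it stands, this is equivalent to requiring systolic ≤180 and (systolic ≥140 or diastolic >90). Readings such as 170/85 and 135/95 stay eligible. The investigator should decide at the same time whether a diastolic ceiling is also wanted.

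The cost is one line of text. If 180 was meant as a general ceiling, no intended patient is lost. If it was not, patients with systolic >180 and diastolic >90, probably few, become ineligible.

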### Exclusion criteria

2.4

The patients will be excluded if they meet 1 of the following criteria:

with secondary hypertension;with severe complications, such as cardiovascular events, endocrine disorders, renal, and hematopoietic system disease;with comorbidities including cancer and mental illness;pregnant or lactating women;having skin infections near the specified acupoints;with insomnia caused by external environment disturbances;with severe chronic obstructive pulmonary disease and bronchial asthma;with severe neurological dysfunction;with alcohol abuse or drug dependence;who considered by the researcher to be unsuitable for this study.

### Randomization and blinding

2.5

Both patients and evaluators will be blinded to the allocation. After signing the informed consent, the eligible patients will be randomly divided into treatment group (acupuncture group) and control group (sham acupuncture group) at 1:1 ratio. The random coding table (001-158) was used for the allocation, and serial numbers was in accordance to the number of patients. The random coding table will be preserved and managed by the designated personnel. After the patients included in this study, their number is notified by researchers to the designated personnel, who will instruct the patients into treatment group or control group. The researchers will write down corresponding records and follow the allocation.

### Treatment group

2.6

Patients in the treatment group will accept acupuncture for 12 weeks, with 3 times a week. Baihui (GV20), Yintang (GV29), Renying (ST9), Hegu (LI04), and Taichong (LR3) will be used as the main acupoints. Acupuncturists will be allowed to add acupoints based on traditional Chinese medicine syndrome differentiation and treatment. The needles will be inserted into the skin to a depth of 10 to 30 mm, and manually operated (including lifting, inserting, and rotating) until patients report a tingling sensation (Deqi sensation). The needles on GV20 and GV29 will be connected to the G6805-2 Multi-purpose Health Device (Huayi Company, Shanghai, China) with frequency at 2.5 Hz and intensity of 45 mA using continuous wave type. The needles will be kept for half an hour before removal.

### Control group

2.7

Patients in the control group will accept sham acupuncture. A non-invasive placebo control (the Streitberger Placebo-needle) will be used. The acupoints are the same as the treatment group, with no insertion. The electroacupuncture instrument (G6805-2 Multi-purpose Health Device) will be placed beside the patients and connected to GV20 and GV29, without electric pulse. Before removal, the needles will be also kept for 30 minutes.

### Outcome measurement

2.8

#### Primary outcome measurement

2.8.1

The primary outcome will be assessed using PSQI, a self-rating questionnaire designed to assess overall sleep quality. It includes 19 self-rating items and 5 other-rating items. It evaluates sleep quality according to the following 7 aspects over the past month: sleep duration, sleep efficiency, daytime dysfunction, delays in falling asleep, use of medications to sleep, sleep disorders, and overall sleep quality. Each aspect is rated 0 to 3 points, and the accumulated scores of the 7 aspects are 0 to 21 points. The higher score indicates poorer sleep quality. The reliability and validity of the Chinese version have been verified.^[11]^ The PSQI will be evaluated at baseline, during treatment period (at 4, 8, and 12 weeks) and follow-up period (at 1, 3, and 6 months).

#### Secondary outcome measurement

2.8.2

The secondary outcomes are sleep parameters, blood pressure dropping, sleeping pill dosage, Rating Depression Scale (SDS) score, and Self-Rating Anxiety Scale (SAS) score.

The sleep parameters, including sleep efficiency, total sleep time (TST), sleep arousal, arousal index, wakefulness after sleep onset, are obtained by Insomnia Severity Index (ISI) scores and nocturnal polysomnography. ISI^[12]^ is designed to evaluate the insomnia symptoms at day and night. The questionnaire consists of 7 items, and each item scores from 0 to 4, and the total score ranges from 0 to 28. The higher score indicates the worse insomnia. The insomnia is classified to be clinical (0-7 points), mild (8-14 points), moderate (15-21 points), and severe (22-28 points). ISI is a subjective self-report questionnaire, whereas nocturnal polysomnography includes many quantitative parameters (arousal index, wakefulness after sleep onset, TST, etc). The patients’ wrist will be worn with the wActiSleep-BT actigraphy (Actigraph LLC, Pensacola, FL) to record sleep quality by noting sleep arousal, TST, sleep onset time, sleep latency, and sleep efficiency. The ActiLife6 (Actigraph LLC, Pensacola, FL, USA) software is used to analyze sleep status and sleep quality.

Patients will be allowed to take sleeping pill (estazolam, 0.5-2.0 mg) during the trial if have a difficulty in sleeping for 3 consecutive days. They will be asked to write down the dose and time of estazolam on a case report form (CRF).

SAS^[13]^ and SDS^[14]^ are used to assess anxiety and depression. The SAS questionnaire consists of 20 items, including 15 negative and 5 positive descriptions. The total score >40 indicates a state of anxiety, which is more severe with the higher score. The SDS also consists of 20 items, and the standard score is calculated by sorting patients’ answers to the 20 questions, with a total score of 1.25 times the standard score. The cutoff point for depression was 50, and the higher score indicates the higher degree of depression.

### Data collection and management

2.9

Evaluation will be conducted during the screening and preparation phases and then periodically conducted throughout the trial. The screening phase will last for 2 weeks, and general information includes age, sex, height, weight, previous medical history, blood pressure, and medication history. The data collection and time course are listed in Table 1.

**Table 1 T1:** Time course for data collection and follow-up.

Enrollment and allocation	Enrollment and allocation		Treatment period			Follow-up period		
Time point	Screening (−14∼0 d)	Allocation (0 d)	4 wk	8 wk	12 wk	1 mo	3 mo	6 mo
Demographics	X							
Vital signs	X							
Previous medical history	X							
Inclusion/exclusion assessment	X							
Informed consent		X						
Routine blood	X							
Routine urine test	X							
Liver function	X							
Kidney function	X							
Electrocardiograph	X							
Allocation		X						
Treatment		X	X	X	X			
Primary outcome		X	X	X	X	X	X	X
Secondary outcomes		X			X			
Adverse events		X	X	X	X	X	X	X

The primary data of patients are collected, and then transcribed into the CRF by the researcher. The researcher must completely and truly record the data according to the clinical study protocol. Data significantly deviating from the clinically acceptable range must be checked and explained. The completed and verified CRF will be handed over to the relevant personnel for data entry, management and statistics. After the transference, the data on the CRF will not be modified. Results will be personally explained to each participant, and disseminated as articles published in international peer-reviewed journals. To publish, we will adhere to the official eligibility guidelines for authorship, and do not tend to use professional writers.

### Patients’ safety

2.10

All patients will accept blood routine, hepatic, and renal functions tests to identify and exclude the patients with severe heart, liver, or kidney disease after the recruitment and before the random allocation. The acupuncture will be discontinued if patients occur any adverse effects. Adverse events (AE) indicate any adverse medical events that occur in the patients regardless of events are related to the operation or experimental drug in the study. The patients will be informed to contact the doctor to diagnose and treat the AE. Fainting, allergy, and pain may appear in the acupuncture clinical trials.^[15]^ If faints occur, the needles will be pulled out immediately, patients will be returned to supine position, given warm or sugar water, and rest until complete recovery. If allergy or pain occurs, needles are taken out immediately and patients are treated according to the specific situation.

The serious AE (SAE) includes death, life-threatening conditions, severe or persistent incapacity or disability, hospitalization, extension of hospitalization time, and potentially serious events. Whether relating to the trial, any SAE or relevant events must be reported to the research unit within 24 hours. The researcher is responsible for recording and reporting all AE and SAE that occurred during the trial (including a 12-week treatment period and a 6-month follow-up period) since the date of signing the informed consent.

